### Data management

For the randomized cluster trial anonymised data only will be stored on a secure study-specific internet database (MedSciNet). All Investigators and study site staff must comply with the requirements of the Data Protection Act 1998 with regard to the collection, storage, processing and disclosure of personal information and will uphold the Act’s core principles.

Local principal investigators will ensure that the confidentiality of the patients’ data is preserved. As permitted by all applicable laws and regulations, limited participant attributes such as, age or date of birth may be used to verify the participant and accuracy of the participant’s unique identification number. Individual participant data will not be disclosed outside of study staff and will not appear on any reports produced by the sponsor. The following people may also access these records:Study monitors and auditors (including the data monitoring committee), who may work for the sponsor or its authorised representatives, who check that the study is being performed correctly and that the information collected is accurate.National and international regulatory authorities involved in keeping research safe for participants.

Participant information provided by the EQUIPTT-Q questionnaire will be labelled with a unique EQUIPTT-Q identification number. It will not include and patient-identifiable information. In order to arrange the interviews, the contact details (email, phone number) of willing participants will be obtained from hospital records only if the participant has been selected for interview.

Published results will not contain any personal data that could allow identification of individual participants.

A data monitoring committee (DMC), independent from the sponsor, will evaluate outcome data (e.g. adverse neonatal outcomes and maternal hospitalisation) in a blinded fashion at regular intervals through the trial with the ability to report any clinical concerns that may arise from the blinded data. Because of the parallel cluster design, data will only be available on the unmasked results at the end of the trial. Depending on the DMC’s requests, the closed DMC session will be able to consider the results of the primary maternal and neonatal endpoints in both arms of the trial and any Serious Unexpected Adverse Events and form a view on whether it is ethical for the trial to continue.

### Selection of participants

#### Main study inclusion criteria

Pregnant women with symptoms of TPTL (contractions or abdominal pain)Between 23^+ 0^ and 34^+ 6^ weeksCapacity for quantitative assessment of fetal fibronectin and/or transvaginal ultrasonic cervical length if randomised to the intervention group.

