### Randomisation

Randomisation is at the cluster level. Centres have been randomly allocated to receive either intervention or control. Due to there being an odd number of centres, seven sites were allocated to one group and six to the other. Minimisation of the randomisation list was not appropriate for this design but the imbalances between three levels of NICU facility at intervention and control sites were small (4:3, 3:2, and 0:1). TPTL rates were known for 10 sites and the difference between the average rates at control and interventions sites were within chance (72 and 89%).

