### Data analysis

#### Cluster randomised trial

Data analysis will follow the intention to treat principle, according to the planned intervention. Data will be analysed using Stata software Version 14 or later (StataCorp, College Station, Texas) to estimate the size and test for statistical significance of any effects of the intervention on primary and secondary, and analysis will be supervised by the trial statistician, [name]. A per protocol analysis will also be performed, excluding those who are incidentally admitted or treated for reasons unrelated to preterm labour. Treatment effects for binary endpoints will be expressed as risk ratios (relative risk) with 95% CIs, using binomial regression and adjusting for variables used in the minimization process. Risk differences will also be calculated for the primary endpoint. The analysis model will include a random effect for clustering and adjusted standard errors for clustering. Adjustments will also need to be made for differences between cluster populations, such as ethnicity and maternal age. Our primary outcome of inappropriate decisions will be measured per 1000 deliveries.

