### Data collection

Local research staff will prospectively collect data on all available eligible episodes of threatened preterm labour.

Key data for all patients (at control and interventions sites)Hospital numberGestation at presentationQuantitative fetal fibronectin values (if available)Cervical length measurements (if available)Current NICU availabilityIUT attempt planned.Patient characteristics (age, parity, ethnicity, risk factors for preterm labour)Outcome data as outlined above (5.1 and 5.2).

Anonymised participant data will be transcribed on to the study database prepared for the trial by MedSciNet (Stockholm, Sweden).

Anonymous data will be stored on the Preterm Clinical Network (PCN) Database (REC Ref. 16/ES/0093). Identifiers (initials, date of birth, hospital and NHS number) required to ensure accurate outcome data collection will be stored on the separate, but linked, PCN Patient Details Database which is only accessible to local site users.

Women will be followed up until postnatal discharge. Neonates will be followed up to discharge or 28 days (whichever is sooner). Local research staff will monitor expected dates of delivery and ensure timely collection of pregnancy outcomes. Outcome data (medical and economic) will be collected by review of obstetric handheld/electronic notes. Outcome data for women who are transferred outside their local unit will be obtained by contacting the referral hospital. The Emergency Bed Service and Neonatal Transport Service are supportive of the study and can assist us in tracking patients who are not accommodated in their local hospital.

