### Implementing the QUiPP app intervention

In each phase, each cluster will recruit consecutive women with singleton or twin pregnancies presenting between 23^+ 0^ and 34^+ 6^ weeks presenting with symptoms of preterm labour. Eligible participants will be identified at labour ward and day assessment triage by the direct care team and local research support teams. Inclusion and exclusion criteria are defined above.

All sites will receive training on the use of the QUIPP App and management guidance prior to its introduction, and periodically throughout the trial at peaks of staff turnover. This training will be delivered by the trial team at different times and locations to suit each site, for example, at departmental audit meetings and staff induction. Training will be delivered via clinical vignettes which provide opportunity for the clinicians to use the app in a training environment. Aide-memoires such as lanyards and pens are provided to each site to encourage use of the app. The doctor/midwife assessing the woman inputs the gestation, previous history of late miscarriage or preterm birth, quantitative fetal fibronectin value and/or ultrasonic cervical length into the app and the app provides % risk of delivery within 1/2/4 weeks and before 30/34/37 weeks. The exact thresholds for admission or treatment are gestation-dependent and may need to be tailored to individual circumstances. However as a recommendation, our guidance will suggest a 5% risk of delivery within 7 days as threshold for antenatal corticosteroid administration, admission, and/or in-utero transfer. Ultimately however the management decisions following the knowledge provided by the QUIPP app will remain the clinicians’ responsibility. A feedback option is available on the app to directly contact the trial team with specific non-clinical queries. Incentives and competitions will also aim to increase recruitment for the qualitative recruitment.

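### The main-study inclusion list ties test capacity to the intervention arm; read literally, it could leave out untestable women at app sites but not at control sites

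*Protocol article*

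**What the plan says.** All references are to the protocol article.

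- **Main study inclusion criteria.** There are three items: symptoms, gestation, and capacity for "quantitative assessment of fetal fibronectin and/or transvaginal ultrasonic cervical length if randomised to the intervention group". The third is the only one that depends on arm.
- **Randomisation.** Allocation is by cluster and has already taken place: "Centres have been randomly allocated to receive either intervention or control".
- **Implementing the QUiPP app intervention.** "each cluster will recruit consecutive women with singleton or twin pregnancies" in the stated gestation range. The same paragraph adds "Eligible participants will be identified at labour ward and day assessment triage by the direct care team and local research support teams" and "Inclusion and exclusion criteria are defined above".
- **Data collection.** "Local research staff will prospectively collect data on all available eligible episodes of threatened preterm labour". The list of key data covers both control and intervention sites and asks for fibronectin and cervical length only where they are available.
- **Data analysis, Cluster randomised trial.** "Data analysis will follow the intention to treat principle, according to the planned intervention". The primary outcome is to be measured per 1000 deliveries.
- **Trial design.** The app is introduced to whole antenatal units and is meant to cover every affected pregnancy. The six control units receive it in the final phase.

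**The concern.** In a cluster trial where women are identified after the clusters are allocated, the comparison is protected only if the same entry rule applies in both arms. Here one item on the list applies in one arm only, and the staff who apply it know which arm they are in. A woman who can have neither fibronectin nor cervical length measured could be judged ineligible at an app site, whereas the same woman at a control site meets the criteria and is counted.

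Two things are at stake. First, the arms could differ in case mix for a reason unrelated to the app. Second, women whom the intervention did not reach are part of its effect in a pragmatic trial. Leaving them out would hide failure of delivery. Intention to treat does not help, because it protects only women who were entered.

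**Working it through.** **Step 1: does any other text override the arm-conditional item?**

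- Consecutive recruitment does not, because the same paragraph refers back to the inclusion list.
- The data collection rule does not, because it covers eligible episodes.
- Intention to treat does not, because it starts from the women entered.
- Recording test values only where available, at both kinds of site, suggests that women without a given result are expected in the data. This pulls against a literal reading but does not say that a woman with neither test at an app site is kept.
- The inclusion list for the women's experience study repeats the symptom and gestation items without the capacity item, although its participants come from the trial. The two lists are therefore not aligned.

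The text permits one-sided exclusion and nowhere rules it out.

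**Step 2: inputs for the size of the effect.**

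- Overall rate of inappropriate decisions: 25%, the control figure in Sample size. It refers to admission decisions only, whereas the primary outcome also includes transfer decisions.
- u, the share of women who can have neither test: not given, assumed 5% to 20%.
- b, the rate of inappropriate management among them: not given, assumed 10% to 40%.
- No app effect, and untestable women left out at app sites only.

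The plan's own sample size is not in question. With 580/13 = 44.6 women per cluster and an intra-class correlation of 0.030, the design effect is 1 + 43.6 × 0.030 = 2.31. A cluster-level t calculation (11 degrees of freedom, 7:6 split, two-sided 5% assumed) gives 81.5% power for 25% versus 10%, close to the stated 80%.

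**Step 3: formulas.**

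Per woman, the rate among those kept at app sites is a = (0.25 − u·b)/(1 − u), and RR = a/0.25.

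Per 1000 deliveries, taking the denominator as all deliveries at the unit (an assumption), exclusion removes events but leaves the denominator alone, so RR = 1 − u·b/0.25.

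**Step 4: results under no app effect.**

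| u | b | a | RR per woman | RR per 1000 deliveries |
|---|---|---|---|---|
| 5% | 40% | 0.23/0.95 = 24.2% | 0.97 | 1 − 0.02/0.25 = 0.92 |
| 10% | 40% | 0.21/0.90 = 23.3% | 0.93 | 1 − 0.04/0.25 = 0.84 |
| 20% | 40% | 0.17/0.80 = 21.25% | 0.85 | 1 − 0.08/0.25 = 0.68 |
| 20% | 25% | 0.20/0.80 = 25% | 1.00 | 1 − 0.05/0.25 = 0.80 |
| 20% | 10% | 0.23/0.80 = 28.75% | 1.15 | 1 − 0.02/0.25 = 0.92 |

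Per woman, the direction depends on whether b is above or below 25%. Per 1000 deliveries, the ratio is below 1 whenever u and b are both above zero.

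For u = 20% and b = 40%, the per-woman risk difference is −3.75 points. With 580 women and the design effect above, the two-sided type I error is about 11% (normal approximation).

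**Step 5: with one entry rule in both arms,** a = 25%, both ratios are 1.00, and the target of 580 does not change.

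**The case against.** The strongest reply is that the item is a site condition in the wrong place. Only centres are randomised, so no woman is ever allocated to the intervention group, and capacity to run an assay or a scan describes a hospital better than a patient. On that reading no individual woman is excluded, and this agrees with consecutive recruitment, with test values recorded where available at both kinds of site, with analysis by planned intervention, and with the aim of covering every affected pregnancy. All 13 centres are carried through the design, so none is shown to have been dropped. This reading is plausible. It does not remove the need for a correction: the line stands among participant criteria, and as a site condition it would still bind only the centres allocated to the app.

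Three further replies stand in part.

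- The criterion says and/or, so a woman would have to be unable to have either test. That makes a 20% share look high, and nothing in the documents supports it.
- Per woman, the ratios at 5% or 10% untestable (0.97 and 0.93) are small beside the planned effect of 10/25 = 0.40.
- A journal article condenses the full protocol, which may say how sites applied the rule. This point, however, concerns wording that the article does state, not something it omits.

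A reader might go further and infer that app sites did exclude untested women and that the primary result is therefore biased towards the app. The documents do not support this. No section tells staff to turn away a woman because her test was not done, and the data list points the other way.

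**Conclusion.** The point holds as a defect of wording that could permit differential inclusion. An arm-conditional item stands in the participant criteria, recruitment and data capture both depend on that list, and nothing states that women with neither test at app sites are kept. Bias is possible, not shown.

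Its size is unknown because u and b are not in the documents. Over the values tried, the per-woman ratio under no effect runs from 0.85 to 1.15, so even its direction is open on that scale. On the per-1000-deliveries scale the direction is fixed in favour of the app, provided the denominator is all deliveries, but the amount still rests on assumed inputs. The 25% base rate is itself borrowed from admission decisions alone.

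**What to change.** 1. Remove the arm-conditional item from the participant criteria, or relabel it as a site condition that applies equally to all centres. The article does not show that all 13 centres met such a condition before randomisation, so that should be stated only if the sponsor can confirm it.
2. State that every consecutive woman who meets the remaining criteria is entered and analysed in her allocated arm, whether or not a test or the app was used.
3. Report the number of women with no test, or for whom the app was not used, by site, as a measure of intervention delivery. This should be separate from the existing secondary outcome on compliance, which concerns whether management recommendations were followed. Without an app result there is no app-derived recommendation to follow.

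The cost is a few sentences and one extra tabulation. The downside is that the app arm will include women whom the app could not reach, so the estimated effect may be slightly smaller. That is the effect of introducing the app to whole units, which is what the trial sets out to measure.

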#### Main study exclusion criteria

Definitive diagnosis of labour (i.e. regular painful contractions with cervical change > 3 cm on speculum or digital examination)Confirmed ruptured membranes (on speculum examination)Significant vaginal bleeding

#### Women’s experience (EQUIPTT-Q) study inclusion criteria

Pregnant women with symptoms of threatened preterm labour (contractions or abdominal pain)Between 23^+ 0^ and 34^+ 6^ weeks

#### Women’s experience (EQUIPTT-Q) exclusion criteria

Unable or unwilling to give informed consentUnder 16 years of ageUnable to understand English language sufficiently to complete the questionnaire booklet

### Implementing the QUiPP app intervention

In each phase, each cluster will recruit consecutive women with singleton or twin pregnancies presenting between 23^+ 0^ and 34^+ 6^ weeks presenting with symptoms of preterm labour. Eligible participants will be identified at labour ward and day assessment triage by the direct care team and local research support teams. Inclusion and exclusion criteria are defined above.

All sites will receive training on the use of the QUIPP App and management guidance prior to its introduction, and periodically throughout the trial at peaks of staff turnover. This training will be delivered by the trial team at different times and locations to suit each site, for example, at departmental audit meetings and staff induction. Training will be delivered via clinical vignettes which provide opportunity for the clinicians to use the app in a training environment. Aide-memoires such as lanyards and pens are provided to each site to encourage use of the app. The doctor/midwife assessing the woman inputs the gestation, previous history of late miscarriage or preterm birth, quantitative fetal fibronectin value and/or ultrasonic cervical length into the app and the app provides % risk of delivery within 1/2/4 weeks and before 30/34/37 weeks. The exact thresholds for admission or treatment are gestation-dependent and may need to be tailored to individual circumstances. However as a recommendation, our guidance will suggest a 5% risk of delivery within 7 days as threshold for antenatal corticosteroid administration, admission, and/or in-utero transfer. Ultimately however the management decisions following the knowledge provided by the QUIPP app will remain the clinicians’ responsibility. A feedback option is available on the app to directly contact the trial team with specific non-clinical queries. Incentives and competitions will also aim to increase recruitment for the qualitative recruitment.

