In terms of guiding management decisions, the majority of cases are assigned a very low-risk (< 1%) by QUiPP app, which clearly indicates a “no admit” strategy. In EQUIPTT, we provide a guidance threshold of 5% risk of delivery within seven days for intervention, based on our previous published work [16]. However, given the other multiple variables that contribute to this decision (such as gestational age), and our intention for the QUiPP app to be a tool to help clinicians make their own decisions, we have refrained from dogmatic recommendation based on absolute thresholds.

We also want to establish if use of the QUIPP app reduces women’s anxiety and/or helps her to come to decisions about her care that she is happy with. Women may have different preconceptions about the significance of symptoms of TPTL and varying perspectives on consequences of admission and or transfer, such as financial anxieties and separation from family, friends and other children [11]. Furthermore, the use of an app to guide clinical management is new to healthcare practice. Given the importance of shared decision-making emphasized by the Montgomery ruling [17], women’s views regarding its application in threatened preterm labour will be central to the future development of the QUIPP app.

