#### **Hypothesis:** The implementation of the QUIPP app and management algorithm will decrease inappropriate management for TPTL

### Trial design

EQUIPTT is a cluster randomised controlled trial (incorporating a parallel group design) across 13 obstetric centres. This design was chosen as for this scale of protocol intervention (in an emergency situation), it would be challenging to randomise at participant level, affecting uptake and generalisability of the findings, and individual clinicians cannot be randomised to varying decision-making with individual patients.

The pragmatic approach was taken to introduce the QUIPP app to entire hospital antenatal units, as standard practice for all clinicians, and all affected pregnancies. Using this parallel cluster studies have the added value of limiting the time-bias which occurs with a stepped wedge design. Also, unlike in a crossover design, the intervention does not need to be retracted from the cluster, avoiding contamination bias. Individuals within a cluster tend to have more similar outcomes than across clusters. The similarity in the outcomes of individuals within a cluster within a time period is typically measured by the within-cluster within-period intra-cluster correlation coefficient. If this is not factored into the power calculation and analysis, the effectiveness of the intervention may be exaggerated [18].

All 13 centres will provide data related to the principal outcome under their current practice in a six-week pre-intervention data collection period. Following randomisation, the centres will use intervention (using the QUiPP app) or control (routine management) for a nine-month analysis period. In the final phase of the trial, the intervention will be introduced in the 6 control units. Following this, data will be collected for a further six weeks across all 13 sites, in order to equally incentivise all sites to participate. The QUIPP app approach will be adopted as standard practice in all sites if successful. A list of the study sites is available from the authors on request.

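### Women are identified after their centre's arm is known, by unmasked staff using a symptom criterion; uneven case-finding could shift the per-woman result, in a direction that depends on the denominator

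*Protocol article*

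**What the plan says.** **Order of events.** Under Randomisation: "Centres have been randomly allocated to receive either intervention or control". Under Trial design: "Following randomisation, the centres will use intervention (using the QUiPP app) or control (routine management) for a nine-month analysis period". Every woman in the analysis period therefore presents after her centre's arm is in force.

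**Who identifies women, and how.** Under Implementing the QUiPP app intervention: "Eligible participants will be identified at labour ward and day assessment triage by the direct care team and local research support teams". The symptom criterion is "Pregnant women with symptoms of TPTL (contractions or abdominal pain"), within a gestation window of 23+0 to 34+6 weeks.

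**Completeness of capture.** The implementation section says that "each cluster will recruit consecutive women with singleton or twin pregnancies". The Data collection section says: "Local research staff will prospectively collect data on all available eligible episodes of threatened preterm labour".

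**Analysis.** The Cluster randomised trial section plans risk ratios by binomial regression, with risk differences for the primary endpoint. It also says that the primary outcome will be expressed per 1000 deliveries. On case mix it says: "Adjustments will also need to be made for differences between cluster populations, such as ethnicity and maternal age".

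**Baseline.** All 13 centres supply data for six weeks before the intervention period.

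**The concern.** Randomising centres balances the populations that present, within the limits of 13 units. It does not protect the step at which a presenting woman is recognised and recorded as a case. Here that step follows allocation, is taken by people who know the arm, and turns on a symptom that leaves room for judgement.

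The article reports that "the majority of cases are assigned a very low-risk (< 1%) by QUiPP app". A woman who is not admitted and delivers more than seven days later counts as an appropriate admission decision. If app sites record more women with mild symptoms than control sites do, those women enlarge the per-woman denominator and add few inappropriate decisions. The app-arm proportion then falls without any change in how comparable women are managed. The two case-mix variables named as examples, ethnicity and maternal age, do not measure how risky the presentation was, so adjusting for them would not remove the shift.

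**Working it through.** **Inputs from the article.** Inappropriate admissions of 25% v 10%, ICC 0.030, 13 clusters, about 580 women and 80% power (Sample size); 6 control and hence 7 app centres (Trial design). Two-sided alpha of 0.05 is stated for the questionnaire study and is assumed here for the primary outcome.

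**Assumed inputs, not in the article.** *f* is the extra low-risk women at app sites as a share of usual entrants. *r* is the inappropriate-decision rate among them.

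**Step 1: reproduce the planned figure.**
- Cluster size: 580/13 = 44.6. Design effect: 1 + (44.6 − 1) × 0.030 = 2.31.
- Women per arm: 6 × 44.6 = 267.7 control and 7 × 44.6 = 312.3 app.
- SE = √{2.31 × [0.25 × 0.75/267.7 + 0.10 × 0.90/312.3]} = 0.0478. Noncentrality: 0.15/0.0478 = 3.14.
- A noncentral t on 13 − 2 = 11 df (critical value 2.201) gives power of 81.5%, against 80% stated. The model agrees with the plan's own calculation, which is on a per-woman scale.

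**Step 2: per-woman scale, no app effect.** The true rate is 25% in both arms. The observed app rate is (0.25 + *f* × *r*)/(1 + *f*). With *r* = 5%:

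| Extra women *f* | App rate | Risk ratio | Shift (points) | Two-sided rejection |
|---|---|---|---|---|
| 0 | 25.0% | 1.00 | 0 | 5% |
| 20% | 0.260/1.2 = 21.7% | 0.87 | 3.3 | 8.8% |
| 30% | 0.265/1.3 = 20.4% | 0.82 | 4.6 | 12.5% |
| 50% | 0.275/1.5 = 18.3% | 0.73 | 6.7 | 21.5% |

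Rejection uses the Step 1 model with the total held at 580. Nearly all of it favours the app: at *f* = 50%, 21.4 of the 21.5 points.

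**Step 3: sensitivity to *r*.** At *f* = 30%, *r* of 2%, 5% and 10% gives shifts of 5.3, 4.6 and 3.5 points. The direction on this scale is stable; the size depends on the assumptions.

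**Step 4: what the whole planned effect would need.** Solving (0.25 + *f* × *r*)/(1 + *f*) = 0.10 gives *f* = 0.15/(0.10 − *r*). That is 150% extra women at *r* = 0 and 300% at *r* = 5%. Dilution alone is an implausible source of the full 15-point effect. At 30% extra it would supply 4.6/15, or about 31% of it.

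**Step 5: per-1000-deliveries scale.** Deliveries do not change when more women are identified, so only the numerator moves. The ratio is 1 + *f* × *r*/0.25. With *r* = 5% it is 1.04, 1.06 and 1.10 at *f* = 20%, 30% and 50%. With *r* = 0 it stays at 1.00. Extra low-risk women cannot lower the app-arm rate on this scale.

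**The case against.** **The direction is not fixed.** A reader might infer that the bias must favour the app. The article does not support that: it also states a per-1000-deliveries scale for the primary outcome, on which the same women move the ratio slightly the other way. This objection stands. The per-woman reading remains live because the sample size, the risk ratio and the risk difference all use it.

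**Different prompting by arm is not stated.** A reader might infer that control staff receive no training or reminders. The implementation section gives training and aide-memoires to all sites. Training comes before the app's introduction, and control units get the app only in the final phase, so prompting at app sites alone during the nine months is a reasonable inference, but still an inference.

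**Control sites need not miss women who go home.** A reader might infer that they mainly notice those admitted or transferred. The article places identification at triage, in every cluster and phase, with the same key data collected in both arms. Nothing requires a woman to be admitted, tested or entered in the app before she is counted.

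**Consecutive recruitment is the stated rule.** It narrows the scope for selection, and all available need not mean that staff may choose. It remains an aim carried out by unmasked staff, and the two phrases are not equivalent.

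**Silence is not a defect.** Screening logs, completeness checks and the final covariate list may be in the full protocol or SAP, and the named adjusters are only examples. Their absence from the article is not counted here. The point rests on the identification route that the article does fix.

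**Conclusion.** The concern holds as a preventable risk of bias. The article fixes a sequence in which allocation is known before identification, the identifiers are unmasked, the entry criterion is open to judgement, and the capture rule is worded in two ways. It does not show that uneven case-finding occurred or will occur.

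On the per-woman scale, 20% to 50% extra low-risk women at app sites would create an apparent reduction of 3.3 to 6.7 points with no app effect, and would raise the two-sided false-positive chance from 5% to about 9% to 22%. These figures rest on assumed values for the extra share and the 5% rate. On the per-1000-deliveries scale the ratio would be 1.04 to 1.10. The direction is therefore settled only once the denominator is. The change is worth making because it is cheap.

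**What to change.** 1. In both the six-week baseline and the nine-month period, have existing local research staff at all 13 sites list participants from labour-ward and day-assessment attendance records. Include every attendance at 23+0 to 34+6 weeks that meets the symptom criterion, subject to the existing exclusions, whether or not the woman was tested, entered in the app or admitted.
2. In the Data collection section, change all available to all, so that it agrees with consecutive recruitment.
3. Report identified women per 1000 deliveries by arm and period. A rise in one arm relative to its own baseline would signal differential case-finding.
4. Add gestation at presentation, parity and risk factors for preterm labour to the primary model. All three are already among the key data.
5. Report the primary result on both the per-woman and the per-1000-deliveries scales.

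The cost is wording changes and modest extra record review. No new participants or procedures are needed.
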